#### Definition of internal target volume and planning target volume

The internal target volume (ITV) will be used to account for respiratory motion. Four-dimensional CT may be employed, ideally with the acquisition additionally 3D CT images at natural end-inhale and end-exhale. The ITV is the union of the GTV-P and GTV-N contoured on each component 3D CT dataset from the four-dimensional CT acquisition to form the envelope that encompasses the motion of the GTV for a complete respiratory cycle [19–21]. The internal margin will be 0.5 cm in the superior-inferior direction and 0.3 cm in the axial plane. The setup margin will be 0.5 cm in all directions. No margin reduction will be allowed even when using IGRT. The final PTV will be obtained by expanding the ITV by the setup margin.

#### Radiation therapy dose prescription

The total dose will be 60 Gy in 30 fractions of 2 Gy. The treatment plan will be normalized so that 95% of the PTV is covered by the prescription dose. The maximum dose to 0.1 cm^3^ should not exceed 110%. 3D conformal radiation therapy or intensity modulated radiation therapy will be used. All radiation doses will be calculated with heterogeneity corrections taking into account the density differences within the irradiated volume (e.g. air, soft tissue, or bone).

### Statistical analysis

All analysis will be performed using Statistical Analysis System (SAS 9.4, Cary, NC, USA). This is a pilot study with a convenience sample of 50 participants for Aim 1 (approximately 5–10 lymph nodes per patient) and the first 20 participants who undergo radiation therapy treatment for Aim 2. The analysis will include node-based analysis and patient-based analysis.

#### Aim 1: node-based analysis

Descriptive statistics will summarize the location and the number of positive cases for each lymph node using CT (where the test positive is defined as a lymph node short axis diameter > 1 cm), PET (where the test positive is defined as that SUV > 3.0), and DECT (where the test positive is defined as that the iodine is < 2.5 mgI/mL). To address clustering, we will perform a multilevel model test. The diagnostic power will be summarized by the area under the curve at receiver operating characteristic analysis (AUC), comparing CT and PET, CT and DECT, as well as PET and DECT. Multilevel models will be used to estimate the probability of a positive, which will be used to estimate the empirical AUC. The following additional analysis will be done to further understand the performance of CT, PET, and DECT. First, the Cohen’s κ statistics will be used to assess the concordance between CT and PET, DECT and PET, and DECT and CT. Second, for patients with known disease status, the AUC will be evaluated comparing CT and PET, and DECT and PET, using the complete PET/CT examination and the pathological specimens, if available, as a reference standard for lesion detection and characterization.

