### Study objectives

The overall goal of this project is to investigate the diagnostic performance of integrated PET/DECT imaging in determining the thoracic nodal status of patients with SCLC or NSCLC and its impact on target volume delineation for IGRT planning.

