### Data analysis

#### Tumor detection

Before analysis, images from each patient will be separated into three groups (PET, CT, iodine-map) corresponding to three different datasets. Images will be all reviewed on a picture archiving and communication system workstation. Two radiologists with > 5 years of experience will independently analyze the number of pulmonary lesion(s), mediastinal and hilar adenopathies, and distant metastases in the three datasets in separate reading sessions. Lymph nodes will be considered to be involved if they demonstrate a SUV > 3.0 on PET, a short axis ≥ 10 mm in diameter on CT, or a iodine reduction on the iodine-map (mean iodine concentration < 2.5 mgI/mL). For each lesion, the CT diameter, CT attenuation, iodine concentration, and SUV will be measured using a region of interest drawn by the radiologist. Radiologists will be blinded to patient identity, lesion number, and the results of other imaging studies. To avoid recall bias, the time interval between each of the reading sessions will be at least two weeks. After this blind evaluation, the study coordinator will review all images and match the imaging findings with the lesions marked by each reader in each dataset. The reference standard will be the complete evaluation of the PET/CT performed separately from the individual components above. Discrepancies between radiologists will be handled in consensus.

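### Every Aim 1 contrast pairs single modalities, so Aim 1 does not estimate the nodal performance of integrated PET/DECT or what iodine adds to PET/CT

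*Protocol article*

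**What the plan says.** The Study objectives section of the protocol article sets out to "investigate the diagnostic performance of integrated PET/DECT imaging in determining the thoracic nodal status of patients with SCLC or NSCLC". Key points and Discussion present the expected gain as an improvement on PET/CT, and Discussion expects it to matter most where SUV is borderline.

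For the reading, Tumor detection states that "images from each patient will be separated into three groups (PET, CT, iodine-map) corresponding to three different datasets", and the readers count findings in each dataset in separate sessions. For each lesion the CT diameter, iodine concentration and SUV are measured. On the reference it says: "The reference standard will be the complete evaluation of the PET/CT performed separately from the individual components above".

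Aim 1: node-based analysis defines positivity for each modality alone: short axis for CT, SUV above 3.0 for PET, iodine below 2.5 mgI/mL for DECT. It then plans three sets of contrasts:
- AUC, "comparing CT and PET, CT and DECT, as well as PET and DECT";
- Cohen's κ, to "assess the concordance between CT and PET, DECT and PET, and DECT and CT";
- for patients with known disease status, "the AUC will be evaluated comparing CT and PET, and DECT and PET", against the complete PET/CT and pathology where available.

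Aim 2: patient-based analysis compares PET/CT with PET/DECT by a signed-rank test on GTV measures in 20 patients.

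**The concern.** The objective concerns a combined test, and the natural comparator in this protocol is PET/CT. The Aim 1 analysis contains neither combination as an index test: PET/CT enters only as the reference standard. The multilevel model is introduced to handle clustering and to estimate the probability of a positive. Nothing says that it combines SUV with iodine.

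The hypothesis about borderline SUV is a statement about iodine given SUV, and a PET-versus-DECT contrast cannot test it. DECT alone may be worse than PET and still improve PET/CT, or better than PET and add nothing. At stake is whether the pilot returns an estimate of its own stated quantity.

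**Working it through.** **Objective against planned contrasts**

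| Analysis | Pairs compared | Combined PET/DECT included? |
|---|---|---|
| Aim 1, AUC | CT–PET, CT–DECT, PET–DECT | No |
| Aim 1, κ | CT–PET, DECT–PET, DECT–CT | No |
| Aim 1, AUC with known disease status | CT–PET, DECT–PET | No |
| Aim 2, signed-rank test | PET/CT–PET/DECT | Yes, but on GTV in 20 patients |

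CT–DECT is in the first two rows and missing from the third.

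**Plan's own figures.** There is no power calculation to reproduce. The convenience sample of 50 patients with about 5 to 10 nodes each implies 50 × 5 = 250 to 50 × 10 = 500 nodes.

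**Do single-modality figures determine the combination?** The document gives no accuracies, so these sensitivity/specificity values are assumed: PET 0.80/0.85, CT 0.60/0.75, DECT 0.70/0.75. For one threshold, AUC = (Se + Sp)/2, which gives 0.825, 0.675 and 0.725. For an either-positive rule with unknown dependence:
- Se lies between max(Se1, Se2) and min(1, Se1 + Se2);
- the false-positive rate lies between max(FP1, FP2) and min(1, FP1 + FP2).

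PET with CT: Se is 0.80 to 1 and the false-positive rate is 0.25 to 0.15 + 0.25 = 0.40, so Sp is 0.60 to 0.75. The AUC runs from (0.80 + 0.60)/2 = 0.700 to (1 + 0.75)/2 = 0.875.

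PET with DECT: the same limits apply, so the AUC again runs from 0.700 to 0.875.

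The difference can therefore lie anywhere from −0.175 to +0.175, and either combination can fall below or above PET alone (0.825). Under conditional independence:
- PET with CT: Se = 1 − 0.20 × 0.40 = 0.92, Sp = 0.85 × 0.75 = 0.6375, AUC 0.779;
- PET with DECT: Se = 1 − 0.20 × 0.30 = 0.94, Sp = 0.6375, AUC 0.789.

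**Does the planned κ close the gap?** Let a and b be the probabilities that both tests are positive in involved and uninvolved nodes. Then Se = Se1 + Se2 − a and the false-positive rate is FP1 + FP2 − b, so the AUC depends on b − a. Given the two positivity rates, κ fixes only the prevalence-weighted average of a and b. It narrows the range but does not settle it.

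**Does the combining rule matter?** Take assumed, conditionally independent values of PET 0.80/0.85 and DECT 0.85/0.90.
- Either positive: Se = 1 − 0.20 × 0.15 = 0.970, Sp = 0.85 × 0.90 = 0.765.
- Both positive: Se = 0.80 × 0.85 = 0.680, Sp = 1 − 0.15 × 0.10 = 0.985.

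That is a spread of 29 points in sensitivity and 22 in specificity from the rule alone. No CT value enters, so this says nothing about PET/DECT versus PET/CT.

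**Reference standard.** If the complete PET/CT defines the truth, a node called by iodine and not by PET/CT counts as a DECT false positive whatever its true state. PET/CT as an index test would be scored largely against itself.

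**The case against.** - *The trial does compare PET/DECT with PET/CT.* It does, in Aim 2. A reader of Aim 1 alone might infer that the comparison is absent from the whole trial, and that would be wrong. But the Aim 2 outcome is a volume in 20 patients, not nodal accuracy, so the gap in Aim 1 remains.
- *This is a pilot, and describing the iodine map beside PET and CT is a reasonable first step.* This stands as a reason to keep the single-modality pairs. A pilot may be imprecise, but it should still estimate the quantity it names.
- *The contrast may be in an analysis plan that is not shown.* The article lists its Aim 1 contrasts explicitly, and the list does not match its objective. That is a mismatch in stated content, not a condensed detail.
- *Adding the contrast is not enough.* This stands in full. Against the complete PET/CT as reference, added value from iodine would be biased towards nothing and could give a misleading negative.
- *The contouring section already supplies an either-positive rule.* A reader might infer this from Virtual simulation and 3D treatment planning, but the wording there is and/or, one sentence covers both PET/CT and PET/DECT, and no size criterion appears. It does not define two rules that can be compared.
- *The missing CT–DECT pair in the reference-standard analysis is minor.* Agreed. PET serves as the common comparator there, and adding the pair is a matter of consistency.

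**Conclusion.** The concern holds for Aim 1. As listed, its contrasts do not estimate the nodal performance of integrated PET/DECT or the increment from iodine over PET/CT. This conclusion rests on the text and needs no assumed number.

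The size of the defect cannot be stated. The ranges of 0.700 to 0.875 and the 29- and 22-point spreads rest on assumed accuracies. They show that single-modality figures leave a combination undetermined. They do not measure how far PET/DECT differs from PET/CT in this trial, and should not be cited as if they did.

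The gap can be repaired without new measurements if, as the Tumor detection text appears to intend, nodes count among the lesions on which SUV, diameter and iodine are recorded. It should be corrected, but it does not undermine the trial as a whole.

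**What to change.** 1. Make the main Aim 1 contrast a paired, derived comparison on the same nodes: the change in AUC from SUV + short axis to SUV + short axis + iodine. Resample patients, not nodes, in the bootstrap, and correct both AUCs for optimism.
2. Estimate it in nodes with pathological confirmation. Label any result against the complete PET/CT as agreement, not accuracy.
3. Keep the single-modality pairs as secondary, and include CT versus DECT in the reference-standard analysis.
4. Defer paired sensitivity and specificity of combined rules until the nodal criteria are reconciled. Virtual simulation and 3D treatment planning uses and/or with no size criterion, Tumor detection uses a short axis of at least 10 mm on CT, and Aim 1 uses more than 1 cm.

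The cost is protocol and analysis-plan wording, a little programming, and lower precision in the confirmed subset. Pathology is used only where available, so the result describes the nodes that were sampled. The derived contrast measures what the iodine value adds. It does not replace a fused PET/DECT reading, which is not among the planned nodal reads and would cost more.

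### The Aim 1 AUC is scored on a model's probability of a test-positive result; most readings of that rule distort the AUC, and the measured node values should be the score

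*Protocol article*

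**What the plan says.** Aim 1 of the protocol article covers 50 patients with "approximately 5–10 lymph nodes per patient". The section *Aim 1: node-based analysis* first sets one cut-off per modality for descriptive counts: for CT "the test positive is defined as a lymph node short axis diameter > 1 cm", for PET an SUV above 3.0, and for "DECT (where the test positive is defined as that the iodine is < 2.5 mgI/mL". It then names a multilevel model to deal with clustering, makes the AUC the summary of diagnostic power for three pairwise comparisons (CT with PET, CT with DECT, PET with DECT), and says how that AUC is obtained: "Multilevel models will be used to estimate the probability of a positive, which will be used to estimate the empirical AUC".

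Disease status enters this section only afterwards, in an additional analysis restricted to patients whose status is known, with the complete PET/CT examination and any pathology as reference. The section *Tumor detection* also names the complete PET/CT evaluation as the reference standard, and it records the raw values: "For each lesion, the CT diameter, CT attenuation, iodine concentration, and SUV will be measured using a region of interest drawn by the radiologist".

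**The concern.** An empirical AUC needs two things per node: a score that ranks the nodes and a reference that says which are diseased. The plan takes the score from a model for the probability of a positive. The only meaning of positive in that section is a test result beyond a cut-off. The text does not say whether the model's outcome is the test result or node status, whether the modality enters as a yes/no result or as its measured value, or whether the prediction includes the patient's random effect.

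These choices decide what the AUC means. The patient effect is estimated from the same nodes that are then ranked, so including it credits the test with information about the patient that the image did not supply. A yes/no predictor reduces the ROC curve to one operating point. A model of test positivity does not target disease at all. At stake is the comparison between modalities, which is the main output of Aim 1.

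**Working it through.** The plan gives no expected AUC, so there is no figure to reproduce. The check asks what each reading does to a test whose true AUC is known.

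**Inputs from the protocol article.** 50 patients and 5 to 10 nodes each, so 50 × 5 = 250 to 50 × 10 = 500 nodes; one cut-off per modality; continuous values measured per lesion.

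**Assumptions (not in the document).** Latent-scale intraclass correlation (ICC) of node status 0, 0.23, 0.50 or 0.66; node prevalence about 0.30; true AUC of the continuous measurement 0.50 (useless) or 0.80; cut-off at specificity 0.60, 0.80 or 0.95.

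**Method.** 120 simulated trials per setting. Random-intercept logistic model by maximum likelihood with 15-point quadrature. AUC as the Mann-Whitney statistic against node status.

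**Reading 1: the outcome is test positivity (the section's own definition).** At ICC 0.50, a test with true AUC 0.80 scores 0.67 to 0.71 when the model holds only the patient effect. With node status as a covariate it scores 0.98 to 0.99, which is circular because the answer is in the score. A repeat with a separately written fit gave 0.72 to 0.75 and essentially 1.00, so the direction is firm but the second decimal is not.

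**Reading 2: the outcome is node status, the predictor is the yes/no test, and the patient effect is included.**

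| ICC | True AUC 0.50 | True AUC 0.80 |
|---|---|---|
| 0.23 | 0.81 | 0.85–0.87 |
| 0.50 | 0.88–0.89 | 0.91–0.92 |
| 0.66 | 0.92–0.93 | 0.94–0.95 |

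The true gap between the two tests is 0.80 − 0.50 = 0.30. At ICC 0.50 and specificity 0.60 the observed gap is 0.916 − 0.884 = 0.032; at specificity 0.95 it is 0.912 − 0.884 = 0.028. With a continuous predictor plus the patient effect, the values at ICC 0.50 are 0.94 and 0.89. At ICC 0 a useless yes/no test still scores 0.66 to 0.71, partly because tiny fitted patient effects break ties. Part of the excess is therefore in-sample reuse of the data and not clustering as such.

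**Reading 3: the outcome is node status, the predictor is the yes/no test, fixed effects only.** One threshold gives AUC = (Se + Sp)/2. Under an equal-variance binormal model with AUC 0.80, the separation is d = √2 × Φ⁻¹(0.80) = 1.190 and Se = 1 − Φ(Φ⁻¹(Sp) − d):

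- Sp 0.60: Se 0.826, AUC (0.826 + 0.60)/2 = 0.713
- Sp 0.80: Se 0.636, AUC (0.636 + 0.80)/2 = 0.718
- Sp 0.95: Se 0.325, AUC (0.325 + 0.95)/2 ≈ 0.637

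The simulation agrees (0.71, 0.72, 0.64) and shows no inflation from clustering. Two tests with the same true AUC can differ by 0.718 − 0.637 = 0.081 through cut-off placement alone.

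**Reading 4: the outcome is node status, the predictor is continuous, fixed effects only.** A true 0.80 gives 0.80. With one linear predictor in the right direction, the probability ranks nodes exactly as the raw value does. A useless test drifts to 0.52–0.53 because the model picks the direction from the data.

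**Raw measurement as the score, no model.** Mean 0.80 for a true 0.80 and 0.50 for a true 0.50, at every ICC. Clustering then affects only the variance.

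**The case against.** The best defence is that the text does not commit to any of the harmful readings. The cut-offs stand in the sentence on descriptive counts, the AUC sentence repeats none of them, and continuous values are recorded, so Reading 4 is open. Conditional prediction is nowhere stated. A reference standard is named under *Tumor detection*. And "This is a pilot study with a convenience sample of 50 participants for Aim 1", with no power claim, so limited precision is expected. Much of this stands: the size of the problem cannot be known until the reading is fixed.

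It does not remove the point. The sentence states a method: it puts a model between the measurement and the AUC. Under the one benign reading that step is redundant, and under the others it distorts. Pilot status excuses wide intervals but not an unclear target.

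Two stronger inferences are tempting and should not be drawn. One is that the AUC is both inflated by clustering and driven by the cut-off, and so says nothing about diagnostic power. Inflation needs the patient effect in the prediction; cut-off dependence needs the yes/no predictor without it. With the patient effect the AUC hardly moves with the cut-off (0.916, 0.915, 0.912 at ICC 0.50), and (Se+Sp)/2 still measures accuracy at one operating point. The other is that nodes will be treated as independent in the intervals for the AUC differences and for κ. The article says only that κ "statistics will be used to assess the concordance between CT and PET" and the other pairs, describes no interval, and does name a multilevel model for clustering. Interval methods are commonly left to the full protocol or SAP, which is not shown.

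**Conclusion.** The point holds in a limited form. The score behind the Aim 1 AUC is badly fixed: as worded it leans on a cut-off definition of positive, and the AUC it yields depends on choices the sentence leaves open. For the same test with true AUC 0.80, the readings span about 0.64 to 0.99. If the patient effect is included, the contrast between a useless and a good test falls from 0.30 to about 0.03 at ICC 0.50.

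These figures rest on assumed ICC, prevalence and true AUC, and each belongs to a different reading, so they must not be summed. They show how far the result can move, not how far it will. Confidence is high that the sentence needs replacing and moderate at best about the size of any bias. It should be corrected before analysis, but it is not a flaw in the study design or the data collected.

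**What to change.** Replace the sentence with:

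> *For each modality the empirical AUC is computed from the continuous node measurement (short axis, SUV, and iodine concentration with lower values indicating involvement) against the node-level reference. Clustering of nodes within patients is handled in the variance of the AUCs and their differences, by a clustered-ROC method or a bootstrap that resamples patients.*

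Report sensitivity and specificity at the stated cut-offs as secondary results. For that, the two CT definitions must be reconciled: *Aim 1* has a short axis above 1 cm, while *Tumor detection* has "a short axis ≥ 10 mm in diameter on CT", so a node of exactly 10 mm is classed differently. The AUC from measured values is not affected by this.

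Cost: a change of wording, a little programming and slightly wider intervals. No new data are needed, because all three measurements are already planned for each lesion.

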#### Aim 2: patient-based analysis

We will evaluate the impact of DECT and FDG-PET image fusion on treatment planning in 20 patients out of the 50 recruited who will receive radiation therapy at our institution. Descriptive statistics will be used to summarize GTV measure. A Wilcoxon Signed-Rank test will be used to explore the statistical difference of the above measurements between PET/CT and PET/DECT.

## Discussion

This prospective clinical trial has been designed to assess the role of the first integrated PET/DECT system for staging and IGRT planning in lung cancer. In detail, we plan to investigate the role of PET/DECT in determining the nodal status of SCLC and NSCLC, and IGRT planning [22, 23].

We speculate that the accurate quantification of iodine uptake obtained with the DECT could improve the morphological delineation of lesions, differentiating normal tissue and atelectasis from lung cancer [22, 24], allowing a smaller volume of lung to be treated with IGRT. In addition, recent data suggest that it could improve the detection of pathological lymph nodes [21], which is particularly relevant when SUV results are borderline [25, 26].

Knowledge gained during this study may potentially allow for an improvement in PET/CT accuracy for lung tumor and thoracic adenopathy detection, and for a more accurate definition of the treatment target decreasing the radiation dose delivered to normal tissue.

## Abbreviations

^18^F-FDG: ^18^F-fluorodeoxyglucose
3D: Three-dimensional
CT: Computed tomography
DECT: Dual-energy computed tomography
GTV: Gross tumor volume
GTV-N: Gross tumor volume, nodes
GTV-P: Gross tumor volume, pulmonary
IGRT: Image-guided radiation therapy
ITV: Internal target volume
NSCLC: Non-small-cell lung cancer
PET: Positron emission tomography
PVT: Planning target volume
SCLC: Small-cell lung cancer
SUV: Standard uptake value
